### Data analysis

Parametric and non-parametric tests are used at the individual level to compare the intervention and control group at baseline, depending on the distributions of the quantitative variables. The X²-test is used in qualitative variables. Repeated measure analyses will be used to evaluate differences in the primary outcome variables body weight, BMI, WC and fat mass between pre- and post-intervention in the intervention and control group. Because preference randomization occurred at the level of SHO and not at the level of the individual patient, cluster effects will also be examined. The analyses of the primary outcomes will be performed on an intention to treat (ITT) basis. Secondary outcome variables will be evaluated per protocol. A P-value ≤0.05 is considered statistically significant. For statistical analyses, SPSS®19 will be used.

To examine the cost-effectiveness of the intervention, a Markov decision-analytic model assuming a public payer perspective will be constructed to project health outcomes and costs of the health promotion intervention compared with usual care. Overweight and obesity are substantial risk factors for the high prevalence of type 2 diabetes and cardiovascular disease in individuals with MD[35,36]. Therefore, the Markov model will be used to estimate, for both the intervention and control group, the development of cardiovascular disease and type 2 diabetes over time and the associated costs. The time horizon will be a 10-year period. In both the intervention and control arm several health states will be included in the Markov model. All future costs and health outcomes will be discounted respectively at 3% and 1.5% annually. The costs will be calculated by analyzing the direct health care costs and the costs of the program. The direct health care costs include hospitalization, medication, GP consultations, and other health professionals costs. The program related resource use (staff time, materials) and resulting costs will be calculated making a distinction between the resource used and costs related to the research purpose and those related to the intervention itself.

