### Sample size calculation

The sample size calculation is based on an average change of the primary outcome body weight of 3.5 kg between the intervention and the control group at the end of the study. This change is based on the results of a previous literature review performed by the research team on the effectiveness and cost-effectiveness of lifestyle interventions on PA and eating habits in people with MD [12]. Cluster randomized trials require larger sample sizes than the individually randomized design. This can be explained by the fact that observations on individuals in the same cluster tend to be correlated, and so the effective sample size is less than the total number of individual participants. This reduction in effective sample size and the degree of correlation within clusters is known as the intraclass correlation coefficient (ICC) [20,29]. As no ICC for this kind of intervention in people with MD was found in the literature, an assumption was made by multiplying the sample size with a design factor of 1.5. A sample size of 371 participants in each group would provide a sample large enough to detect a difference in mean body weight change of 3.5 kg across the two groups with 80% power at a significance level of 0.05.

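### The plan does not commit the primary tests to account for clustering by sheltered housing organisation; if they were left unadjusted, the two-sided error would be about 7% to 11% on the plan's own design factor, not 5%

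*Protocol article*

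**What the plan says.** The Study design and setting section makes the SHO the unit of allocation. The Sample size calculation section gives the reason why this matters, namely that "observations on individuals in the same cluster tend to be correlated, and so the effective sample size is less" than the head count. No ICC was found in the literature, so "an assumption was made by multiplying the sample size with a design factor of 1.5".

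The Data analysis section covers three things relevant here:

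- **Baseline.** Parametric and non-parametric "tests are used at the individual level to compare the intervention and control group at baseline".
- **Primary outcomes.** Body weight, BMI, waist circumference and fat mass are to be evaluated by repeated-measures analyses, by intention to treat. The section does not say how the SHO enters these analyses.
- **Clustering.** "Because preference randomization occurred at the level of SHO and not at the level of the individual patient, cluster effects will also be examined".

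The decision rule is "A P-value ≤0.05 is considered statistically significant".

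**The concern.** The article does not leave clustering to another document: it states how clustering will be handled, and the statement is too weak. The word for the handling is examined, and it is set alongside the named primary analysis rather than inside it. Nothing says that the p-value or interval reported for a primary outcome will contain an SHO term, or what follows from the examination.

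If patients are analysed as independent when SHOs were allocated, the standard error of the arm difference is too small. The stakes are the main p-value and interval of all four primary outcomes. The wording also leaves room to choose between an adjusted and an unadjusted result after seeing both. Correlation within SHOs is plausible here, because the programme is given in group sessions led by each SHO's own staff.

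**Working it through.** **The plan's own figure.** The sample size section gives "A sample size of 371 participants in each group" to "detect a difference in mean body weight change of 3.5 kg" "across the two groups with 80% power at a significance level of 0.05". No standard deviation is stated, so 371 cannot be reproduced, only back-solved. Sidedness is not stated either; two-sided is assumed. With n = 2(1.960 + 0.842)² SD² / 3.5² = 2 × 7.849 × SD² / 12.25 per group:

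- SD 13.87 kg gives 246.5, so 247, and 247 × 1.5 = 370.5, so 371.
- SD 17 kg gives 370.3, so 371, before any inflation.

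The article says that the factor was applied, so the first reading is the natural one. Neither affects what follows, which uses only the factor 1.5.

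**Inputs.**

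- Design factor 1.5 (Sample size calculation).
- Significance level 0.05 (Data analysis), taken as two-sided.
- SHOs: 14 + 2 = 16 intervention and 5 + 4 = 9 control, 25 in all. One control SHO had no interested patients, leaving 8 control SHOs and 24 overall (Baseline study population characteristics). The section on study duration gives 14 intervention groups; I use the 16 from the recruitment account.
- Patients with baseline data: 201 + 83 = 284, a mean of 284/24 = 11.83 per SHO.

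**Formulas.** Design effect DE = 1 + (m − 1) × ICC, where m is the mean cluster size. Actual two-sided error of a test that ignores clustering = 2 × [1 − Φ(1.960/√DE)]. An unadjusted interval has 1/√DE of the correct width.

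**Reading A: the 1.5 holds at the realised cluster size.**

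- Implied ICC = 0.5/10.83 = 0.046.
- 1.960/√1.5 = 1.600, so the error is 0.1095, about 11%.
- Width ratio 1/√1.5 = 0.82.
- A simulation of an individual-level t-test with 16 and 8 SHOs and 201 and 83 patients gave 10.5%. A t-test on SHO means in the same simulation gave 5.8%.

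**Reading B: the 1.5 was meant for the planned size.**

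- 2 × 371 = 742 patients over 25 SHOs is 29.7 per SHO, so ICC = 0.5/28.7 = 0.017.
- At 11.83 per SHO, DE = 1 + 10.83 × 0.0174 = 1.19.
- 1.960/√1.19 = 1.80, so the error is 0.072, about 7%. Width ratio 0.92.

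**Sensitivity to an assumed ICC, at 11.83 per SHO.**

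| ICC (assumed) | DE | Actual two-sided error |
|---|---|---|
| 0.01 | 1.11 | 6.3% |
| 0.02 | 1.22 | 7.6% |
| 0.05 | 1.54 | 11.4% |
| 0.10 | 2.08 | 17.4% |

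**Could the examination itself decide whether to adjust?** The plan does not say that it would. The calculation shows why the replacement text should rule it out. Take a one-way F-test for an SHO effect with 24 equal SHOs and 284 patients (23 and 260 degrees of freedom, 5% critical value 1.57). Under a given ICC the statistic is a central F multiplied by 1 + 11.83 × ICC/(1 − ICC). Its power is about 11% at ICC 0.01, 19% at 0.02 and 47% at 0.046. Even if Reading A is true, the test would miss the clustering more than half the time.

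**The case against.** The strongest reply is that the text is terse rather than wrong. It gives allocation by SHO as the reason for looking at cluster effects, which is compatible with an SHO random effect in the primary model, and a full protocol or analysis plan may spell this out. Part of this stands. The article does not say that the primary tests ignore clustering, and the detailed random-effects structure is properly left to a fuller document. What does not fall away is that the sentence describes an additional look, so carrying it out as written is consistent with unadjusted primary p-values.

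Four stronger readings are tempting and are not supported:

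- **That the primary tests run on individuals.** The individual-level wording applies only to the baseline comparison. For the primary outcomes the level is unstated.
- **That a non-significant cluster effect will be dropped.** No such rule appears.
- **That the analysis contradicts the sample size section.** Both acknowledge clustering; the analysis wording is weaker, not opposed.
- **That the effect passed to the cost-effectiveness model is too optimistic.** Ignoring clustering understates uncertainty and does not systematically enlarge the estimate. The article does not say that the trial's standard error enters the Markov model.

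The individual-level baseline p-values in Tables 1 and 2 share the problem, but they are openly labelled and no stated primary inference depends on them. That is a secondary matter.

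**Conclusion.** The concern holds as a failure to commit. The document makes repeated-measures analyses the test of the primary outcomes and does not bind their p-values and intervals to account for the SHO, although the SHO is the allocation unit and the sample size relies on a design factor of 1.5.

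The size is conditional on the primary test being unadjusted, which the document does not state. On that condition the error is about 11% if 1.5 applies at the realised cluster size and about 7% if it was set for the planned size. The 1.5 is itself an assumption. The calculations take a two-sided test and a common ICC across arms. They use patients with baseline data, so later dropout would change the mean cluster size.

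The nominal 5% also presumes comparable arms. Of the 25 SHOs, 14 + 5 = 19 chose their arm, so no modelling of clustering by itself secures the error rate for the effect of treatment.

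**What to change.** Replace the sentence on examining cluster effects with a commitment along these lines:

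- The primary comparison for each primary outcome is a linear mixed model on the 10- and 36-week values, with arm, visit and arm-by-visit effects and adjustment for the baseline value.
- Random effects are included for SHO and for patient.
- The SHO term stays in the model whatever its p-value.
- Degrees of freedom use a small-sample method, such as Satterthwaite, suited to 24 SHOs.
- The ICC is reported for each primary outcome.

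The baseline comparison can be presented descriptively, without individual-level significance tests.

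The cost is a change of wording. A mixed-model procedure in the statistical package already named is enough. Intervals will be wider: relative to an unadjusted analysis, by a factor of about √1.19 = 1.09 to √1.5 = 1.22 on the two readings above, before the small-sample correction. The change puts the standard errors right; it does not deal with selection bias from SHOs choosing their arm, and the report should say so.

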## Methods and design

### Aim of the study and hypotheses

The aim of the study is to evaluate the effectiveness and cost-effectiveness of a health promotion intervention targeting PA and healthy eating in people with MD living in sheltered housing. We hypothesize that:

· Between baseline and the end of the intervention and after a 6-month follow up period, significant differences in the primary outcomes ‘body weight’,‘Body Mass Index’ (BMI), ‘waist circumference’ (WC), ‘fat mass’ between the intervention and control group will be identified;

· Between baseline and the end of the intervention and after a 6-month follow up period, significant differences in the secondary outcomes ‘quality of life’ (QOL), ‘PA levels’, ‘eating habits’, and ‘psychiatric symptom severity’ between the intervention and the control group will be identified;

· The health promotion intervention is cost-effective.

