### Study duration and intervention components

The study period consists of an intervention period of 10 weeks followed by a post-intervention period of six months. In addition to treatment as usual, the intervention groups (n = 14) receive the 10-week health promotion program targeting PA and healthy eating. In the intervention group the following intervention components are offered:

· Psycho-educational and behavioral group sessions

This part of the program consists of 10 group sessions in a 10-week period and includes discussions on PA and healthy eating, problem solving, written exercises, quizzes and plans to increase PA levels and to stimulate a more healthy eating behavior. All participants in the intervention group receive the same information in the same format. The program is delivered by the mental health professionals working in the intervention SHOs.

· Supervised exercise

In the same 10-weeks period a weekly 30-minutes supervised walking session is organized. These sessions are also led by one or more mental health professionals.

· Individual counseling

During the 10-week intervention period, all participants in the intervention group receive individual support from the mental health professionals (for example motivation to persist, discussing of experiences).

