#### Secondary outcome measures

Changes in PA are assessed using the Dutch long version of the self-administered International Physical Activity Questionnaire (IPAQ), as this questionnaire appears to be a reliable and valid PA measurement tool [31]. The analysis of the IPAQ is based on self-reported data. Therefore, PA levels are also measured using pedometers as a more objective tool. The Yamax Digiwalker SW-200 (Yamax, Tokyo, Japan) is used as this is known as accurate and reliable for counting steps [32]. Dietary habits of the participants are assessed using an adapted version for adults of the “Young Children’s Nutrition Assessment on the Web ”[33]. Quality of life is assessed using the SF-36 Health Survey questionnaire. Finally, psychiatric symptom severity is assessed through the use of the Brief Symptom Inventory (BSI). This questionnaire is considered as a reliable and a valid tool useful in patient groups with different psychiatric diagnoses [34].

Data on all primary and secondary outcome measures are collected at baseline and at 10 weeks. At the end of the study (at 36 weeks) only data on body weight, WC and fat mass will be collected and BMI will be calculated. At that time participants will be asked to only complete again the SF-36 Health Survey.

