### Ethics

Permission to perform the study was obtained from the Ethics Committee of the University Hospital of Ghent (Belgium). Written consent for participation is obtained from all participants. Participation in the study is voluntary and all participants are informed that the data analysis will be anonymous and that they could withdraw from the study at any time. A reward (pedometer) for the participants in the intervention group who completed the program was foreseen.

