## Baseline study population characteristics

A schematic overview of the recruitment process is shown in Figure 3. Twenty-five SHOs were interested to participate. Fourteen of these expressed a preference to serve as intervention group, while five preferred to serve as control group. Six expressed no preference neither for the intervention nor for the control group. These six were randomly assigned to the intervention group (n = 2) and to the control group (n = 4). In one of the SHOs serving as controls no patients were interested to participate.

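### Per protocol is the only analysis stated for the secondary outcomes, which exposes those comparisons to selection after allocation; the article does not show its size or direction

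*Protocol article*

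**What the plan says.** In Data analysis, two consecutive sentences assign different analysis sets. For the primary outcomes: "The analyses of the primary outcomes will be performed on an intention to treat (ITT) basis". For the rest: "Secondary outcome variables will be evaluated per protocol". No reason is given for the difference, the per-protocol set is not defined, and no second analysis of the secondary outcomes is mentioned.

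The secondary outcomes are not presented as exploratory. Aim of the study and hypotheses expects "significant differences in the secondary outcomes ‘quality of life’ (QOL), ‘PA levels’, ‘eating habits’, and ‘psychiatric symptom severity’ between the intervention and the control group". Under Secondary outcome measures, activity is measured by questionnaire and pedometer, diet by questionnaire and symptoms by the BSI. For quality of life: "Quality of life is assessed using the SF-36 Health Survey questionnaire". All are taken at baseline and 10 weeks; of these, only the SF-36 is repeated at 36 weeks.

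The programme belongs to one arm. Study duration and intervention components says: "In addition to treatment as usual, the intervention groups (n = 14) receive the 10-week health promotion program targeting PA and healthy eating" (the count in that sentence plays no part here). The Ethics section treats completion as a status within that arm: "A reward (pedometer) for the participants in the intervention group who completed the program was foreseen". It also tells participants that "they could withdraw from the study at any time".

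**The concern.** A per-protocol set normally keeps those who followed the assigned treatment sufficiently. Here only intervention participants have something to follow: ten group sessions, a weekly supervised walk and individual counselling. Excluding non-adherers would therefore thin one arm, while the control arm keeps the people who would not have attended had they been offered the programme. The two groups compared would then differ by a selection made after allocation.

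This selection could plausibly be related to outcome. The article's Discussion lists the mental disorder itself, medication side effects and poor motivation as barriers to taking part in such programmes. Each could also bear on how activity, diet, quality of life and symptoms change over ten weeks.

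At stake is whether a significant result on a secondary hypothesis can be attributed to the programme. Activity and diet are also the behaviours through which weight is meant to change. Analysing them in one set of patients and weight in another makes the chain from behaviour to weight harder to read, though not impossible.

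**Working it through.** **No plan figure to reproduce.** The article gives no expected adherence, no non-completion rate and no sample size for any secondary outcome. Its 371 per group concerns body weight and does not enter this point. The 29 of 313 candidates (9.3%) who withdrew did so before the baseline measurement, so that is not an adherence rate either.

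**Inputs from the article.** Participants with baseline data: 201 intervention, 83 control (Table 1). Design factor: 1.5 (Sample size calculation). Allocation of SHOs: "Fourteen of these expressed a preference to serve as intervention group, while five preferred to serve as control group", so 14 + 5 = 19 of 25 (76%) chose their arm and 6 of 25 (24%) were randomised.

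**Assumed inputs.** The share excluded from the intervention arm, and how completers and non-completers differ in *change* from baseline for reasons unrelated to the programme.

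**Step 1: simple bias.** Let p be the share excluded, and C and N the mean change in completers and non-completers. The whole-arm mean is (1 − p)C + pN. Keeping only completers shifts the arm mean by C − [(1 − p)C + pN] = p(C − N).

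- p = 0.2, C − N = 0.2 SD: 0.2 × 0.2 = 0.04 SD
- p = 0.2, C − N = 0.5 SD: 0.2 × 0.5 = 0.10 SD
- p = 0.4, C − N = 0.2 SD: 0.4 × 0.2 = 0.08 SD
- p = 0.4, C − N = 0.5 SD: 0.4 × 0.5 = 0.20 SD
- C − N = 0: bias 0 for any p

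If C − N is negative, the shift has the same size and the opposite sign.

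**Step 2: effect on the false-positive rate.** Assume no true effect and a normal selection model. A share d drops out of the intervention arm only, and ρ is the correlation between propensity to complete and change in the outcome. With λ = φ(z_d)/(1 − d):

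- bias = ρλ
- variance in completers: v = 1 − ρ²λ(λ − z_d)
- SE = √{1.5 × [v/(201(1 − d)) + 1/83]}

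Worked case, d = 0.20 and ρ = 0.3: λ = 0.280/0.8 = 0.350; bias = 0.3 × 0.350 = 0.105 SD; v = 1 − 0.09 × 0.350 × (0.350 + 0.842) = 0.962; SE = √{1.5 × [0.962/160.8 + 1/83]} = 0.164. The two-sided type I error at a nominal 0.05 is then 0.098.

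| d | ρ | bias (SD) | implied C − N = bias/d | type I error |
|---|---|---|---|---|
| any | 0 | 0 | 0 | 0.050 |
| 0.20 | 0.1 | 0.035 | 0.175 | 0.055 |
| 0.20 | 0.3 | 0.105 | 0.525 | 0.098 |
| 0.30 | 0.3 | 0.149 | 0.497 | 0.144 |
| 0.40 | 0.1 | 0.064 | 0.160 | 0.066 |
| 0.40 | 0.3 | 0.193 | 0.483 | 0.201 |
| 0.40 | 0.5 | 0.322 | 0.805 | 0.476 |

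The rows with ρ from 0.1 to 0.3 correspond roughly to the 0.2 to 0.5 SD difference of step 1. The last row goes well beyond it and is only an outer illustration.

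**Step 3: what ITT changes.** With all 201 and 83 participants analysed as assigned, the shift p(C − N) is zero by construction. The confounding from 19 of 25 SHOs having chosen their arm remains.

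**The case against.** The strongest reply is that the article does not say who is excluded. Per protocol might have been meant loosely, for participants in either arm with questionnaires at both visits; that rule would apply to both arms. Definitions of analysis sets are commonly left to a full protocol or SAP, which is not shown. This stands as a limit: one-sided exclusion is inferred from the usual meaning of the term and from controls having no programme. It does not remove the point, because the choice of per protocol is itself stated and contrasts with ITT in the sentence before. If available data in both arms was meant, the sentence says something else and needs correcting.

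A reader might go further and infer that every secondary effect will be overstated even if the programme does nothing. The article does not support that. Outcomes are framed as changes from baseline, so a stable difference in level between completers and non-completers largely cancels; bias needs a difference in change. Less ill completers could also have less room to improve on the BSI or SF-36, which would push the bias towards no effect.

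Two further replies stand. All four primary outcomes are ITT. The cost-effectiveness result does not visibly depend on this set either, since QALYs come from a Markov model with disease-state utilities and no use of the trial's SF-36 data is stated. It is also true that ITT cannot give a fully randomised comparison here. That is no reason to add a second, patient-level selection that the choice of analysis can avoid.

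**Conclusion.** The point holds as an exposure to bias, not as a demonstrated bias. Per protocol is the only analysis stated for outcomes that carry formal between-group hypotheses. On the term's usual meaning it selects on post-allocation behaviour in one arm.

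Size and direction cannot be taken from the article. The bias is zero if completion is unrelated to change. It is about 0.04 to 0.20 SD under the assumed 20% to 40% exclusion and 0.2 to 0.5 SD difference in change. Over roughly that range, with a design effect of 1.5, the false-positive rate runs from about 0.055 to 0.20. The low end is negligible and the high end is not. Every figure in that range rests on assumed non-completion and an assumed link to outcome.

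This should be fixed, but it is not critical: it limits what can be claimed for the secondary outcomes and leaves the primary analysis untouched.

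**What to change.** Replace the sentence on secondary outcomes with one to this effect: the main analysis of each secondary outcome includes all participants in the arm assigned to their SHO, uses all available data and accounts for clustering by SHO; a per-protocol analysis, with its set defined before the data are examined, is supportive only.

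The model needs to be named. The article says only that repeated measures analyses will be used for the primary outcomes and that cluster effects will be examined, so there is no specific cluster-adjusted model to carry over.

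The text change is small and adds no measurements to the planned schedule. There are two costs. Estimated effects may look smaller. The gain also depends on participants who stop the programme still being assessed at 10 weeks and, for the SF-36, at 36 weeks; the article does not say whether they are, so the plan should say so. If they are not, ITT would be so in name while the same people remain missing.
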